## Abstract

**Background:**

Cooking interventions have increased in popularity in recent years. Evaluation by meta-analyses and systematic reviews show consistent changes in dietary quality reports and cooking confidence, but not of cardiovascular (CVD) biomarkers. Interventions evaluating or reporting behavioral mechanisms as an explanatory factor for these outcomes has been sparse. Moreover, evaluations of cooking interventions among communities with health disparities or food access limitations have received little attention in the literature.

**Methods:**

This study will occur over two phases. Phase 1 will assess acceptability among the target population of African-American adults living within an urban food desert. Phase 2 will consist of a 6-week cooking intervention delivered at a community kitchen setting. Pre and post intervention visits for clinical examinations and biomarker collection will be conducted, as well as dietary and cooking skill assessments. Primary outcomes include cooking behavior and feasibility measures. Secondary outcomes are related to dietary quality, psychosocial factors, CVD biomarkers, and food environment measures.

**Discussion:**

This study seeks to demonstrate feasibility of a community-based cooking intervention and to provide necessary information to plan future interventions that identify cooking behavior as an outcome of participation in cooking interventions among African-American adults, especially in relation to dietary and biomarker outcomes.

**Trial registration:**

This study was registered at ClinicalTrials.gov (NCT04305431) on March 12, 2020.

## Background

Disparities in cardiovascular disease (CVD) morbidity and mortality among African-Americans persist despite advances in risk factor identification and evidence-based management strategies [1]. Studies suggest risk factor reduction positively attenuates the mortality disparity between African-Americans and other racial/ethnic groups [1]. Closing the CVD disparity gap may require attention to more proximal causes of CVD that lower risk factors, including cardiovascular health behaviors such as dietary intake and physical activity.

Dietary behaviors consist of eating habits, food/nutrition choices, and meal preparation or cooking behavior. Among dietary behaviors, national survey data show those who frequently prepare meals at home have a better diet quality overall determined by higher vegetable intake [2] and lower daily calorie intake [3]. Observational studies show possessing a greater number of cooking skills is linked to healthier food choices [4]. However, cooking and meal preparation at home have decreased in the United States (U.S.) [5], while there has been an increase in consumption of food away from home [6]. Consequently, it is possible that the inability for Americans to meet the recommended guidelines for fruit and vegetable consumption [7] may be a public health consequence of the reduction in cooking at-home and shift to convenience foods.

The trend toward less cooking is also occurring in racial minority populations in the U.S., with African-Americans reporting cooking dinner at home less than other racial/ethnic populations [8]. An updated analysis of U.S. Adult Time Use survey data showed African-American men were the racial and gender group least likely to report engaging in meal preparation activities [9]. Our own group’s NHANES (National Health and Nutrition Examination Survey) analysis of cooking frequency among African-Americans found that employment, income, and self-perceived diet quality were significant determinants of home cooking frequency [2]. Cross-sectional studies from an African-American population in a Baltimore food desert show that self-efficacy and beliefs are also contributors and are positively associated with cooking frequency and type of home cooking method [10, 11].

When evaluating published cooking interventions, studies among African-Americans from faith-based and community settings show successful self-report of dietary quality for improved fruit and vegetable consumption and Dietary Approaches to Stop Hypertension (DASH) score post cooking interventions [12–15]. This is in contrast to nutrition education studies that allowed participants to make their own food for the DASH diet [16]. In these studies, African-Americans were less likely as compared to Non-Hispanic Whites to be adherent to the DASH eating plan [16]. The differing results between cooking intervention studies and free-living studies suggest an important role of cooking interventions on implementation of a cardiovascular protective dietary plan among African-Americans.

Cooking can be defined as a goal-directed behavior, where the goal is to create a meal/dish to satisfy nutrition needs or tastes for oneself or others. Two theoretical frameworks related to goal-directed behaviors that pertain to current understanding of facilitators and barriers for cooking are the social cognitive theory (SCT) and the theory of planned behavior (TPB). Both theories include individual factors related to home cooking, including self-efficacy (Fig. 1). Self-efficacy is defined as a person’s belief in their capabilities to produce designated levels of performance that exert influence over events that affect their lives. It is an important construct in determining someone’s motivation for a health behavior change. In terms of cooking behavior, this can transfer into self-efficacy surrounding cooking tasks, such as preparing a meal or cutting up an ingredient, to shopping for particular food items, to determining meals based on desire to change or improve one’s health. These self-efficacy influences are built into cooking interventions that include aspects of personal agency, also known as food agency [17].

**Fig. 1 Fig1:**
[figure not shown]
Diagram of cognitive processes and constructs involved in theory of planned behavior and social cognitive theory adapted for hypothesized cognitive processes involved in home cooking. Constructs from SCT are represented by rectangles. Constructs from TPB are represented by circles. Constructs common to both are represented by triangles. Adapted from Koenings M and Arscott S, 2013

### Gaps in the literature

Recent systematic reviews of community level cooking interventions found significant improvements in attitudes, cooking self-efficacy, and healthy dietary intake and participation in cooking interventions [18, 19]. However, no significant outcomes are reported for cardiometabolic risk factors, including blood pressure and body mass index (BMI) within these reviews. Although methodological variation and high risk of bias from studies were identified, the findings are similar to earlier systematic reviews of cooking interventions [20]. The current literature thus leaves several questions to be addressed. If dietary intake changes and cooking efficacy changes are occurring, what is the behavioral pathway for these changes? Furthermore, what behavioral pathways may be needed or are sufficient for the expected biomarker changes to occur?

A combination of better informed food purchasing for home consumption, better choices when eating out, or more frequent home cooking may lead to dietary benefits, but ultimately may not explain needed or sufficient behavioral mechanisms. For example, practice and modeling are tenants of the SCT construct of self-efficacy. Participants may receive practice and modeling within intervention sessions that contribute to self-efficacy, but may not have these same opportunities transfer to the home environment if home cooking behavior is not the behavior mechanism. Thus, it is conceivable that if opportunities for practice only occur within the intervention, then long-term behaviors needed for cardiometabolic change may not occur. Despite this, most cooking intervention studies only include dietary quality or health outcome variables as the primary outcomes reported [21], not cooking behavior. Furthermore, identification of cooking behavior as a mechanism is important, as cooking has the potential advantage of being more economical [22] or conferring a psychosocial benefit [23] that may be of special benefit to communities disproportionately affected by diet related chronic diseases.

The current gaps in the literature around the role of behavior may also occur because assessing behavioral mechanisms for cooking intervention outcomes can be complex. For instance, the concept of cooking skills is representative of a confluence of skills: perceptual and conceptual, mechanical, academic (knowledge of preparing raw and cooked foods), and cognitive planning skills. Additionally, for each individual, the interplay between these skills may differ based on their intrapersonal or interpersonal experiences. Lastly, the absence of a detectable effect may not result from the cooking intervention being ineffective, but rather could be a consequence of the logistical difficulties in standardizing and evaluating complex health interventions, especially in an experimental process [24]. Ideal participation and engagement level in an intervention to achieve an increase in cooking frequency is not well defined in the literature. Furthermore, it is unclear if participation and engagement level is expected to vary between individuals, or by objectively determined baseline cooking skill.

Feasibility allows for focus on real-world acceptability and implementation, while involving key stakeholders (study participants) at each stage of the exploration process [25]. A feasibility study approach also allows for process evaluations that provide a detailed understanding of complex interventions by examining their implementation, mechanism of impact, and context [26]. In relation to facilitators and barriers to cooking, understanding aspects of feasibility could help inform behavioral mechanisms that can explain cooking intervention results. The purpose of this protocol paper is to present the design and conceptualization of a cooking intervention feasibility study among African-American adults living within a food desert to evaluate home cooking behaviors pre and post a community cooking intervention.

Based on the limited body of evidence regarding the implementation and biobehavioral outcomes of cooking interventions, the aims for the D.C. COOKS with Heart study are to:
Determine feasibility of delivery of cooking behavior intervention for African-American adults at risk for CVD as described by Bowen et al. (25):
DemandAdherence to the sessionsAcceptability (e.g., content and delivery)Practicality (e.g., mode of delivery)Integration/implementation (facilitators and barriers) to home cookingDetermine outcomes of secondary areas of interest related to dietary quality, CVD risk factors, health behaviors, and psychosocial factors in order to gain insight into the relationship of these factors and home cooking behavior.

Table 1 shows specific primary and secondary aims for the study.

**Table 1 Tab1:** Specific study aims

Phase 1	
Primary aims	a) Assess acceptability of the cooking intervention delivery and content (recipes) b) Identify facilitators and barriers to cooking frequency among focus group members
Phase 2	
Primary aims	a) Determine feasibility of the intervention, especially in association with facilitators, or barriers to cooking
Secondary aims	a) Explore the relationship between feasibility measures with intrapersonal, social and built environment factors
	b) Explore the relationship between feasibility measures with dietary quality (24 hour diet recall, Mediterranean Diet Score, Healthy Eating Index scores)
	c) Explore the relationship between feasibility measures with CVD biomarkers and anthropometric measurements

## Study design

The study design uses a feasibility study model with a mixed-method research approach. The study will occur in two phases. Phase 1 will consist of focus groups with the primary aims to identify and assess current facilitators and barriers to cooking behavior in the community to inform the study. Phase 2 will consist of the cooking intervention and clinical assessment visits at baseline and at two follow up periods, 6 weeks and 12 weeks post intervention. Overall, phase 2 will have four different time points: baseline clinical visit (TP_0_), cooking intervention (TP_1_), second clinical visit occurring 6 weeks after the intervention concludes (TP_2_), and a subsequent clinical visit occurring 12 weeks post intervention (TP_3_). The protocol for D.C. COOKS follows the SPIRIT checklist [27]. Table 2 shows the overall study plan and design.

**Table 2 Tab2:** Study plan and timeline

	Phase 1		Phase 2											
Schedule of events and study plan	Enrollment for phase 1	Focus groups (community site)	Enrollment for phase 2	Clinical visit #1 TP_0_	Community cooking class—2-h session weekly for 6 weeks (community site) TP_1_						Home cooking experience	Clinical visit #2 TP_2_	Home cooking experience	Clinical visit #3 TP_3_
Week				− 4 to 0	1	2	3	4	5	6	7-11	12	13-17	18
Eligibility screen	X		X											
Informed consent		X		X										
Focus group discussion		X												
History and physical, vital signs, anthropometrics Blood draw for CVD biomarkers				X								X		X
Interview with study team				X			X			X		X		X
Dietician assessment				X								X		X
AMPS cooking skill assessment				X								X		
Daily cooking journal					X	X	X	X	X	X	X	X	X	X
Participant surveys		X		X								X		X
Community cooking intervention					X	X	X	X	X	X				

## Study population and settings

### Development of D.C. COOKS with Heart

The relevance of a study can be enhanced, and the retention of study participants improved, when community members’ knowledge and experience informs the design of the intervention and dissemination of findings [28]. Community-based participatory research (CBPR) focuses on a research topic of importance to the community and ensures that intervention strategies designed using this approach are compatible with the culture and life circumstances of the target community and population being studied [29, 30].

A previous CBPR cardiovascular health and needs assessment of a sample population from predominantly African-American churches in wards 5, 7, and 8 was conducted through the Heart Health Study in Washington D.C. to develop a community-based behavioral weight loss intervention (Protocol: 13-H-0183; NCT 01927783 PI: [name]). The health and needs assessment screening involved measuring cardiovascular health factors within the church-based population; and evaluated social determinants of health factors that impact weight loss. The original protocol established a community advisory board, Washington, D.C. Cardiovascular Health and Obesity Collaborative Cooking Survey (DC CHOC), to consult on the planning and implementation of the assessment, as well as the interpretation and dissemination of findings from that study.

Results from the community-based cardiovascular health and needs assessment were used to inform the design and implementation of this current community-based protocol. The current study proposal and concept were presented to DC CHOC to evaluate whether members perceived the aims of the study as relevant to the community’s interest with regard to limited dietary choices and to gauge the community’s interest in intervention studies which might improve dietary behaviors among African-Americas living in wards 7 and 8. The committee provided input on intervention location and delivery, including selection of the interventionist.

Both ward 7 and ward 8 represent areas that are historically African-American, and are geographically separated from the rest of the city by the Anacostia River. While the population is diverse in economic and education levels, both communities represent significant economic and health disparities compared with the rest of the city. Both communities have the highest obesity prevalence and cardiovascular-related health events for Washington, D.C. [31], and both are considered urban food deserts. The term food desert refers to geographic areas where most people have limited access to healthy food as defined by (1) located more than half a mile from a grocery store or supermarket or (2) low rates of car access [32]. Limited access to food is a problem that affects millions of Americans every year, and these areas tend to have concentrations of low-income and minority residents, invoking socioeconomic and racial disparities. In 2016, there were 49 grocery stores in D.C. and the average number per ward was six. However, between wards 7 and 8, there are only three grocery stores for more than 140,000 residents [33]. The communities’ location within a food desert therefore limits access to fresh foods that are most often readily used for cooking, which is a limitation that may relate to participation in cooking behavior, and food purchasing choices.

### Study population

Based on the prior CBPR study, the proposed target communities for this study show a need for dietary CV risk reduction based on the risk for obesity, but also on dietary intake. In the aforementioned CBPR study, a low daily fruit and vegetable intake level of 3.2 servings per day was found compared to recommended guidelines of five per day [34]. Given the risk for CV disease, and need for improved dietary intake of fruits and vegetables, identifying ways to lower cardiovascular risk through cooking behavior within these communities may be important. Adults are the focus for this intervention and not family or child-based, because in most families adults are the nutritional decision makers [35].

Discussing health disparities requires attention and justification to how race and ethnicity are conceptualized, described, and utilized within scientific studies [36]. It is important to identify dietary quality among African-Americans, because African-Americans disproportionately live in underserved areas that are subject to social, political, and policy-related pressures that determine their food environments. Thus, the selection of African-Americans in this study stems not because unhealthy diets are intrinsic to African-Americans [37, 38], but because both wards 7 and 8 are predominately African-American, 92.4% and 92.1%, respectively [39]. Therefore, most adults who are at risk for CV disease within these communities are African-American. Moreover, within our community-based study, selection of one racial/ethnic group allows for focused insight into diet related social determinants and CVD health risks that are related to the experiences of underserved African-Americans in similar communities.

### Inclusion and exclusion criteria

Participants will be eligible for this study if they are at least 18 years of age, self-identify as African-American, English-speaking, live within the designated neighborhoods of Washington, D.C. (i.e., ward 7 or 8), and self-report a risk factor for cardiovascular disease: overweight or obese, type 2 diabetes, pre-diabetes, current or recently (12 months prior) former smoker, and hyperlipidemia.

## Methods

### Study settings

Both the phase 1 focus group and phase 2 intervention sessions will be conducted within ward 7 at a location central to both Washington, D.C. communities of interest for the study, wards 7 and 8.

The clinical setting for the study will be the National Institutes of Health (NIH) Clinical Center (CC), the U.S.’s only hospital devoted solely to clinical research. The hospital is located in Bethesda, MD, a suburb of Washington, D.C. Research participants at the NIH CC are evaluated in both outpatient and inpatient settings. For this study, an outpatient clinic utilized in the prior CBPR study will be utilized for all clinical visit appointments.

### Study procedures

In phase 1 of this study, participants (*n* = 20) will take part in one of two moderated focus groups designed to explore participants’ experiences with food and dietary selections and cooking behavior. Within this phase, participants will also take self-administered surveys related to cooking behavior, non-dietary health behaviors, and psychosocial factors. Open-ended (qualitative) questions for the focus groups were selected to elicit feedback regarding facilitators and barriers to cooking and perceptions about the feasibility of the intervention regarding (1) obtaining food for cooking, (2) use of cooking skills, (3) social norms around home cooking, (4) personal attitudes and knowledge, (5) preferences for recipes/food choice, and (6) preferences for intervention timing. Focus group feedback will also be used to modify the survey, if needed. Data analysis is anticipated to occur over a 1-month time period and the results of data analysis will inform the second phase. Specifically, the data captured from this phase will inform phase 2 in terms of recipe selection for intervention, local locations to source food for the intervention, anticipated concerns about intervention location, and schedule of sessions.

Phase 2 of the study consists of two parts: clinical visits, surveys, and interviews at pre (TP_0_) and post intervention intervals (TP_2_, TP_3_) and the cooking intervention (TP_1_). We will recruit thirty (*n* = 30) participants for this phase. Phase 2 will start with a baseline visit (TP_0_) prior to the intervention start. During this visit, a clinical history and physical examination, objective cooking assessment, dietician interview, and phlebotomy for CVD biomarkers will take place. Following completion of baseline visits for all participants, the community intervention will start with all participants who have completed the initial clinical visit. We estimate that it will take 4 weeks for all participants to complete their baseline visit. Participants will return for the second clinical visit at 6 weeks and 12 weeks post the intervention. To ensure that time of participation and days of follow up in the study are equal among participants, those who enroll and come in for their baseline visit at the earliest time point (week 4) will return for follow up visits prior to participants who completed baseline visits closer to the end of the initial time point (T_0_).

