### Cooking intervention

The 6-week cooking intervention (TP_1_) in phase 2 will be delivered by a chef who is professionally trained, licensed, and certified regarding local food safety regulations. The intervention site will be a community-based kitchen site located within ward 7 or 8. Participants will be divided into two groups of 15. Each group will meet weekly at the kitchen site for a 90-min culinary education session. There will be no group assignment; participants may choose which group to attend, but can only attend one group session per week. The minimum number of participants required for delivery of the intervention will be one participant per session. In case of the need for an emergency medication administration for unknown food allergies, all sessions will be staffed with clinical research team members. Medical students trained in culinary medicine will also be present during each session to assist participants as needed. Table 3 provides an overview of the DC COOKS with Heart cooking intervention sessions.

**Table 3 Tab3:** D.C. COOKS with Heart cooking intervention

Goal	Deliver cooking behavior intervention in a community setting
Type	In-person, chef-led instruction
Duration	6-week intervention with weekly 2-h sessions
Structure of sessions	Introduction and discussion of recipes and ingredients Cooking of recipes in groups Shared meal experience
Assessments	Semi-structured interviews (phone administered) Treatment fidelity Behavior change taxonomy (BCT)

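### Equal time in study and follow-up visits at 6 and 12 weeks after the classes cannot both be delivered when baselines are staggered over 4 weeks

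*Protocol article*

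**What the plan says.** Study procedures gives the baseline period: "We estimate that it will take 4 weeks for all participants to complete their baseline visit". Table 2 places these visits in weeks -4 to 0. The classes have one common start: "Following completion of baseline visits for all participants, the community intervention will start with all participants who have completed the initial clinical visit". Table 3 describes a "6-week intervention with weekly 2-h sessions", and Table 2 puts the sessions in weeks 1 to 6, so the last session falls in the same week for everyone.

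Follow-up is defined by time since the classes. Study design describes TP2 as the "second clinical visit occurring 6 weeks after the intervention concludes" and places TP3 12 weeks after the intervention. Study procedures repeats this: "Participants will return for the second clinical visit at 6 weeks and 12 weeks post the intervention". Table 2 gives single weeks, 12 and 18.

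Study procedures then adds a second aim: "To ensure that time of participation and days of follow up in the study are equal among participants". The means is an order of return, in which people who "come in for their baseline visit at the earliest time point (week 4) will return for follow up visits prior to participants" with later baselines. The week 4 in that sentence is evidently week -4 of Table 2.

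Under Primary outcomes, the cooking diary starts after the initial clinical visit and stops after the last one, with a stated total of 18 weeks.

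**The concern.** A follow-up visit can be held constant relative to baseline or relative to the last class. When baselines are staggered and the classes end together, it cannot be constant relative to both. The article promises both and does not say which gives way.

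The choice matters because TP2 and TP3 are there to show whether cooking practised in class carries over to the home and lasts. Time since the last session is the interval that question depends on. Time in study also includes the wait before any class was held.

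If the equality rule is followed, the labels 6 weeks and 12 weeks cover a range of delays, and the delay follows enrolment order. The Data analysis section compares group means and within-person change by time point, so those delays would be pooled under one label. The measures exposed are those taken at the visit: the AMPS skill assessment (whose only post-intervention measurement is the 6-week visit), the cooking surveys, the diet recall and MEDAS, and the biomarkers.

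**Working it through.** **Inputs**
- Baseline week *b*: from -4 to 0 (Table 2; 4 weeks in Study procedures).
- Last session: week 6 for everyone (Table 2).
- TP2 and TP3: 6 and 12 weeks after the classes (Study design, Study procedures).
- Diary: from baseline visit to last visit, 18 weeks (Primary outcomes).

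**Reproducing the plan's figures.** 6 + 6 = 12 and 6 + 12 = 18, which are the weeks in Table 2.

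**The two intervals.** For a visit in week *V*, time in study = *V* - *b* and time since the last session = *V* - 6. If *V* - *b* is the same for all, *V* moves one-for-one with *b*. A 4-week range in *b* then gives a 4-week range in *V* - 6. If *V* is fixed, *V* - *b* has the 4-week range instead.

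**Case A: visits fixed at weeks 12 and 18.**

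| Baseline week | TP0 to TP2 | TP0 to TP3 | TP2 after last session | TP3 after last session |
|---|---|---|---|---|
| -4 | 16 weeks | 22 weeks | 6 weeks | 12 weeks |
| -2 | 14 weeks | 20 weeks | 6 weeks | 12 weeks |
| 0 | 12 weeks | 18 weeks | 6 weeks | 12 weeks |

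Time in study, and so a diary kept from baseline visit to last visit, runs from 18 to 22 weeks. The stated 18 weeks is true only for a person with baseline at week 0.

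**Case B: time in study fully equal.** The article does not say which total is held constant, so three are shown.

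| Total time in study | TP2, calendar weeks | TP2 after last session | TP3, calendar weeks | TP3 after last session |
|---|---|---|---|---|
| 18 weeks | 8 to 12 | 2 to 6 weeks | 14 to 18 | 8 to 12 weeks |
| 20 weeks | 10 to 14 | 4 to 8 weeks | 16 to 20 | 10 to 14 weeks |
| 22 weeks | 12 to 16 | 6 to 10 weeks | 18 to 22 | 12 to 16 weeks |

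The spread is 4 weeks in every row, and the first-enrolled are always seen soonest after the classes. The 18-week row is the one that agrees with the stated diary total. In that row the first-enrolled have TP2 in week 8, although Table 2 shows a home-cooking period of weeks 7 to 11 before that visit.

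**What stays constant in Case B.** TP2 and TP3 shift together, so each person's TP2-to-TP3 interval is still 6 weeks. The wait from baseline to the first class is not equalised. It still varies by about 4 weeks and is offset at follow-up.

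**The case against.** **Four weeks is an upper bound.** The article states an aim and an order of return, not visit dates. If baselines fill only part of the window, or visits are merely ordered within or near weeks 12 and 18, the spread is smaller. This stands as a limit on size. It does not rescue the text, because the stated equality then fails.

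**Equal baseline-to-follow-up time is a defensible choice for a pre-post comparison.** It is. The fault lies in promising it together with fixed delays after the classes.

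**The 18-week diary could be counted from week 1.** Table 2 does mark the diary from week 1 to week 18. Primary outcomes, however, starts it after the initial clinical visit, which may be up to 4 weeks earlier, so the text and the table still need to be reconciled.

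**The consequence is limited.** This is a single-arm feasibility study whose inference is declared exploratory. Its stated success criterion, more than 50% of participants attending at least 3 of 6 sessions, does not depend on follow-up timing. Diary data are aggregated by study week and can be lined up with the common last session whatever the clinic date. All of this stands.

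**A stronger reading.** A reader might infer that early enrollees are keener, and that fading can therefore never be separated from type of participant. The documents do not support this. Staff telephone identified people and invite them to schedule a visit, and nothing links visit order to motivation. Within-person change from TP2 to TP3 is over the same 6 weeks for everyone, so stable differences between people cancel in it. What does follow from the rule is narrower: in comparisons between people at one visit, delay is aligned with enrolment order.

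**Visit windows and covariates commonly belong to the full protocol or SAP.** Their absence here is not the point. The point is that the article states rules that are incompatible.

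**Conclusion.** The plan is wrong as written: equal time in study and follow-up at 6 and 12 weeks after the classes are incompatible for any staggered baseline with a common end of classes.

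The size is up to 4 weeks, in one place or the other. It appears in time since the last session if equality is enforced, or in time in study and diary duration (18 to 22 weeks) if weeks 12 and 18 are kept. The full 4 weeks assumes that baselines fill the whole window and, in the first case, that equalisation is complete.

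The effect falls on visit-day measures summarised by time point. It does not reach the attendance criterion, and the weekly diary series can be recovered by realignment. It is a scheduling contradiction to settle before visits are booked, and it does not undermine the feasibility result.

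**What to change.** 1. In Study procedures, define TP2 and TP3 by time since the last session, as Study design already does, with a window as narrow as clinic capacity allows.
2. Withdraw the statement that time of participation and follow-up will be equal, together with the order of return that serves it.
3. Restate the diary duration as 18 to 22 weeks, and make its start agree between Primary outcomes and Table 2.
4. Record actual days since the last session and days since baseline at each visit, and use both in the exploratory TP2 and TP3 analyses.

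The cost is a few sentences and two variables derived from visit dates. The downside is that baseline-to-follow-up time will vary by about 4 weeks plus the width of the visit window.

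The window should therefore be tight. A window of plus or minus 2 weeks would put TP2 at 4 to 8 weeks and TP3 at 10 to 14 weeks after the classes, the same spread as the 20-week row of Case B. If slots ignored baseline order, baseline-to-follow-up time could then vary by up to about 4 + 4 = 8 weeks. Such a window would break the link with enrolment order but would not narrow the delays.
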